### Eligibility and inclusion

The inclusion criteria included American Society of Anesthesiologists (ASA) grades I–III adults of both sexes more than 70 years old who were scheduled for surgery lasting up to 60 min, living at home or living in institutions without daily medical care, and able to be contacted by phone during the follow-up period. The exclusion criteria included having been diagnosed with dementia or having a severely impaired psychometric test (Mini-Mental State Examination (MMSE) score <15), any disability that would make the geriatric assessment incomplete (visual, auditory, or disabling apraxia), severe brain pathology (tumor, stroke, Parkinson's disease, etc.), or patients with related contraindications for BIS monitoring (pacemaker, brain surgery, cardiac surgery, or any surgery that prevents the analysis of the BIS under suitable conditions).

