### Statistical analysis

The main outcome will be defined as "the percentage of patients alive without loss of autonomy in the sixth month (26 ± 2 weeks) following surgery." By definition, death will be included as a permanent loss of autonomy of the subject. Secondary outcomes include a comparison of the postoperative complications using Dindo and Clavien's classification, a change in the Frail status (subclassified as robust, pre-frail, and frail) after 6 months according to Fried's scale, and the quality of anesthesia assessed through the total duration in the expected interval of BIS value (40–60), the total duration in too deep anesthesia (defined as a BIS value <40), and the occurrence of a suppression ratio. The period of analysis is only that during general anesthesia. Based on the published data, it is estimated that at 6 months, the mortality in this population will be approximately 8%, institutionalization will be required in one in five of the remaining cases, and in the patients who remain alive without institutionalization, a decline in ADL will occur in one subject in six in 6 months. This leads to an overall proportion of patients who will die or whose level of functioning will deteriorate after a scheduled major surgical intervention of 39.4%. We hypothesize that better control of the depth of anesthesia should reduce this figure by one third. Under these conditions, a sample of 430 patients, equally divided between the two anesthesia groups, leads to a Fisher’s exact test with a risk of first species bilateral of 0.05 to a power of 0.8 to highlight the expected difference, if it exists.

This research will include a randomization of 1:1 between the groups with stratification based upon the frailty status of the subject prior to the surgery, as determined using the phenotypic Fried scale in three categories (robust, pre-frail, and frail) crossed with two surgical risks (minor or major) [19] (Table 1). The randomization list with balancing groups is performed using a computer program; allocation to a group is performed automatically.

**Table 1 Tab1:** Determination of surgical risk (minor or major) in the elderly. (Adapted from Eagle [19])

Usual classification	Type of surgery	Adapted classification in elderly patients
Low Risk	Wall surgery without opening the peritoneal cavity	Low Risk
	Abscess drainage	
	Endoscopies	
	Proctology	
	Plastic surgery	
	Ophthalmic surgery	
Intermediate Risk	Intraperitoneal surgery	Major Risk

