	Laparoscopic surgery	
	Endarterectomy	
	Ear, nose and throat (ENT) surgery	
	Prostate surgery	
	Orthopedic surgery	
	*Intermediate risk in elderly (>70 years old)*	
Major Risk	Intermediate surgery performed in emergency	
	Unstable hemodynamic conditions	
	Vascular surgery (aortic and peripheral) and thoracic surgery	
	Prolonged surgery (>4 h) with high fluid displacement or major bleeding	

A statistical intention-to-treat analysis will compare both groups (manual and automated general anesthesia) after 6 months through the generalized linear mixed model (GLIMM), which considers the type of anesthesia, frailty status, and surgery. A significant threshold at 0.05 is defined, and the software used for the analysis will be either R3.0 or SPSS20. A logistic regression or a multivariable analysis could be performed to establish some predictive factors if relevant. To ensure that the hypothesis was correct compared to observed data, an intermediary analysis is planned after 100 inclusions.

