This hypothesis is supported by numerous studies. First, our group showed that automated anesthesia guided by the BIS sensor outperforms manual anesthesia regarding the duration in the expected range [22]. Therefore, this system seems capable of continuously adapting the posology of anesthetics depending on the immediate needs and eventual hemodynamic events. A sudden drop in cerebral output leads to a decrease in BIS and in site-effect concentrations, allowing a typical titration of drugs. This description was suggested in the case of cardiac arrest with a complete stop in infusion and a restart after recovery. This accurate adaptation to the patient’s needs is very important considering the literature on too deep sedation. The first description was reported in an intensive care unit with a dichotomy between a patient with burst suppression (isoelectric signal) and one without. In addition, an analysis of patients undergoing surgery with this kind of controller demonstrated a more frequent occurrence of isoelectric periods in the elderly without clear risk factors [7]. Different studies on severely ill patients have been performed using an automatic controller of anesthesia, with some publications on lung transplantations and patients in intensive care. Consequently, these results suggest a difference in brain susceptibility, as described with newborns.

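### The two BIS-time outcomes are defined as absolute durations with no denominator, so length of anesthesia adds noise: a large loss of precision for time at BIS 40–60, a smaller one for time below 40

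*Protocol article*

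**What the plan says.** The Statistical analysis section of the protocol article lists three measures of quality of anesthesia among the secondary outcomes. Two of them are durations: "the total duration in the expected interval of BIS value (40–60), the total duration in too deep anesthesia (defined as a BIS value <40"). The third is an occurrence, namely whether any suppression ratio appears. The sentence after the list sets the window: "The period of analysis is only that during general anesthesia". No section expresses the durations as a share of anesthesia time.

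The only model named, for the 6-month comparison, takes in type of anesthesia, frailty status and surgery. Length of anesthesia is not listed. Randomization is stratified by frailty status and by minor or major surgical risk.

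On length of surgery, Eligibility and inclusion admits patients "scheduled for surgery lasting up to 60 min", while the major-risk class of Table 1 includes "Prolonged surgery (>4 h) with high fluid displacement or major bleeding".

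**The concern.** A quality measure should change when control of depth changes and stay put when only the length of the operation changes. A total duration does not do this. Take the same control in two cases, with 75% of time at 40–60 and 15% below 40 (values assumed for illustration). An anesthetic of 60 min then scores 45 min in range and 9 min too deep; one of 240 min scores 180 min and 36 min. The longer case looks better on one outcome and worse on the other, although control was identical.

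These outcomes matter because the Background rests the trial's hypothesis on limiting too-deep anesthesia and burst suppression, and they show whether the controller achieved that. Between-patient variation in case length enters them as noise and makes a difference between arms harder to detect and to interpret.

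**Working it through.** **Inputs from the document.** The outcome definitions above, and 430 patients equally divided, hence 215 per arm. The document gives no SD, effect or power for the BIS-time outcomes, so there is no planned figure for them to reproduce. The 430 belongs to the primary outcome. It does reproduce: 39.4% against 26.3% gives 430 with continuity correction, and exact Fisher power at 215 per arm is 0.802. This has no bearing on the present point.

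**Assumed inputs.** Mean proportion of time in band π, its SD s, and the coefficient of variation c of anesthesia duration. Duration is taken as independent of the proportion. For scale, a uniform spread of 20–60 min has c = (40/√12)/40 = 0.29, and a uniform spread of 20–240 min has c = (220/√12)/130 = 0.49.

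**Formula.** With duration T, proportion P and total time in band D = T × P,

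Var(D)/E(T)² = s²(1 + c²) + π²c².

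On the same scale the difference between arms is unchanged, so the efficiency of total time relative to the proportion is

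RE = Σs² / Σ[s²(1 + c²) + π²c²], summed over the two arms.

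**Worked example, BIS 40–60.** Automated 75% (SD 15 points), manual 70% (SD 20 points), c = 0.3.

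- Automated: 0.0225 × 1.09 + 0.5625 × 0.09 = 0.02453 + 0.05063 = 0.07515. Case length supplies 0.05063/0.07515 = 67% of the variance.
- Manual: 0.04 × 1.09 + 0.49 × 0.09 = 0.0436 + 0.0441 = 0.0877. Case length supplies 50%.
- RE = 0.0625/0.16285 = 0.384.

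**Worked example, BIS below 40.** Automated 15% (SD 12 points), manual 20% (SD 17 points), c = 0.3.

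- Automated: 0.0144 × 1.09 + 0.0225 × 0.09 = 0.01772.
- Manual: 0.0289 × 1.09 + 0.04 × 0.09 = 0.03510.
- RE = 0.0433/0.05282 = 0.820.

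The loss is smaller because the mean proportion below 40 is small relative to its SD, so the π²c² term carries little weight.

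**Range of scenarios.**

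| Band | Means, automated/manual (SDs, points) | RE at c = 0.3 | RE at c = 0.5 |
|---|---|---|---|
| 40–60 | 80/70% (12/18) | 0.306 | 0.137 |
| 40–60 | 75/70% (15/20) | 0.384 | 0.183 |
| 40–60 | 70/60% (20/25) | 0.545 | 0.301 |
| <40 | 12/22% (10/17) | 0.810 | 0.605 |
| <40 | 15/20% (12/17) | 0.820 | 0.621 |
| <40 | 15/30% (12/22) | 0.799 | 0.589 |

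For 40–60, more than half the precision is lost in two of the three scenarios at c = 0.3 and in all three from c = 0.4. At c = 0.2, RE is 0.50 to 0.73. For <40, RE is about one half at c = 0.6 (0.50 to 0.53) and clearly below it at c = 0.8 (0.36 to 0.39).

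**Power at 215 per arm, two-sided 0.05, normal approximation.**

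- 40–60, 75% vs 70%: 0.835 for the proportion; 0.443 (c = 0.3) and 0.240 (c = 0.5) for total time.
- <40, 15% vs 20%: 0.941 for the proportion; 0.891 and 0.793 for total time.

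**Does the planned stratification repair it?** In a simulation of 75% vs 70% at 40–60, with two surgical-risk strata and c = 0.5 within stratum, power for total time was 0.21 unadjusted and 0.25 with the stratum in the model. It was 0.74 with duration as a covariate, and 0.85 for the proportion.

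**The case against.** The strongest reply is that the article is condensed. It never names minutes as the unit, and total duration may be a loose label. The Discussion says of the group's earlier work that "automated anesthesia guided by the BIS sensor outperforms manual anesthesia regarding the duration in the expected range", which could describe a percentage. Adjustment for duration is not excluded and would recover most of the loss. Cumulative time below 40 is also a defensible exposure measure, since the Background links harm to deep anesthesia. Percentages can be derived later from the recording.

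Part of this stands. The exposure argument justifies reporting absolute time below 40, though not using it as the measure of quality, and it does nothing for time at 40–60. That the percentage can be derived later means nothing is lost for good. But the definition as printed is a total with no denominator; if a percentage is meant, the text still needs correcting.

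A reader might infer more than the documents support:

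- **That all the quality outcomes lose most of their precision.** This is shown only for 40–60. For <40 the variance comes mainly from depth control unless duration varies very widely. Suppression is an occurrence; a longer anesthetic gives more opportunity for it, but no size has been calculated.
- **That the comparison is biased.** Randomization, stratified by surgical risk, balances expected duration. At c = 0.35 the chance difference in mean length has a standard error of 0.35 × √(2/215) = 3.4% of the mean, and the precision loss already counts it.
- **That a neutral primary result could not be interpreted.** The <40 contrast, which is closest to the hypothesis, keeps power of 0.79 or more in every scenario tabulated. For 40–60 the larger contrasts (80% vs 70% and 70% vs 60%) keep power above 0.9 at c = 0.3 and about 0.71 at c = 0.5.
- **That surgery is known to run from 60 min to over 4 h.** The eligibility text makes 60 min an upper limit as written, and Table 1 is an adapted risk classification, not an eligibility list.

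**Conclusion.** The point holds for two secondary outcomes, as lost precision and interpretability. Both BIS-time outcomes are stated as absolute totals, and length of anesthesia is neither a divisor nor a named covariate. For time at 40–60 the cost is substantial: about 45% to 69% of the precision at c = 0.3 and 70% to 86% at c = 0.5. For time below 40 it is about 20% and 40%.

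These sizes rest on assumed means, SDs and duration spread, and on duration being independent of the proportion in band. The direction does not depend on those values: under independence, any variation in duration makes RE less than 1. How far duration varies cannot be settled from the article until the eligibility criterion and Table 1 are reconciled. The primary outcome and its sample size are unaffected. The definition should be changed, but the trial's main conclusion does not depend on it.

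**What to change.** In the Statistical analysis section, define both BIS-time outcomes as the percentage of general-anesthesia time with a valid BIS signal spent at 40–60 and below 40, compared between arms with adjustment for the randomization strata (frailty status and surgical risk). Report absolute durations descriptively, including cumulative time below 40 as an exposure measure. Keep suppression as an occurrence and, optionally, also give it as a percentage of anesthesia time. Separately, reconcile the length of surgery in Eligibility and inclusion with Table 1.

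The cost is a sentence or two of wording. BIS monitoring is mandatory for every patient and the Abstract says the anesthesia is recorded, so no new data are needed and the sample size does not change.

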## Discussion

During the preoperative visit, elderly patients and their relatives are often more worried about undergoing general anesthesia, because of the risk of death or memory loss, than about the actual surgical procedure. We expect to demonstrate no impairment in the primary outcome in the automated control of anesthesia with accurate titration to maintain BIS in a tight range in comparison to an eventual relationship between manual control and a change in the postoperative status as it concerns mortality and self-sufficiency. This outcome was chosen because it is clinically relevant and represents a real healthcare challenge. Additionally, the role of anesthesiology remains unclear with regards to postoperative cognitive dysfunction if the depth of anesthesia is controlled. In parallel, this cohort may bring information about the course of the frailty status in the postoperative period. Can pre-frailty be a predictive factor for loss of self-sufficiency in the postoperative course?

The depth of general anesthesia is a common factor that may favor postoperative morbidity in the case of excessively deep sedation. This factor has been investigated in many retrospective studies that described a BIS value below 45 as a risk factor for postoperative death or organ failure [20]. This theory was recently reported as the “triple low” by Sessler et al. [21], i.e., low BIS, low arterial blood pressure, and low volatile agent concentration. However, few prospective studies have been designed to support or reject this hypothesis. Therefore, this randomized clinical trial may provide additional information for a specific population of elderly patients. To limit the variability of different brain susceptibilities to anesthetics in the elderly, each patient will be monitored using the BIS with a common target (BIS in the range 40–60), and anesthesia will be performed only with intravenous drugs to homogenize general anesthesia. Under these circumstances, we hypothesize that a significant decrease in the rate of patients with severe impairment in their autonomy, among patients receiving automated anesthesia compared to manually controlled anesthesia, will occur.

This hypothesis is supported by numerous studies. First, our group showed that automated anesthesia guided by the BIS sensor outperforms manual anesthesia regarding the duration in the expected range [22]. Therefore, this system seems capable of continuously adapting the posology of anesthetics depending on the immediate needs and eventual hemodynamic events. A sudden drop in cerebral output leads to a decrease in BIS and in site-effect concentrations, allowing a typical titration of drugs. This description was suggested in the case of cardiac arrest with a complete stop in infusion and a restart after recovery. This accurate adaptation to the patient’s needs is very important considering the literature on too deep sedation. The first description was reported in an intensive care unit with a dichotomy between a patient with burst suppression (isoelectric signal) and one without. In addition, an analysis of patients undergoing surgery with this kind of controller demonstrated a more frequent occurrence of isoelectric periods in the elderly without clear risk factors [7]. Different studies on severely ill patients have been performed using an automatic controller of anesthesia, with some publications on lung transplantations and patients in intensive care. Consequently, these results suggest a difference in brain susceptibility, as described with newborns.

Elderly patients comprise more than 40% of all surgical patients in the USA per year and generate a very large proportion of healthcare costs, especially in the postoperative period [23]. Studies suggest that frailty predisposes an individual to worsening health status and death and is likely unrecognized in elderly patients prior to surgery. Because relatively minor stressors (e.g., urinary tract infections) may result in major consequences such as increased dependence on caregivers, the need for nursing care, and predisposition to falls and delirium, major stressors such as surgery are likely related to a loss of autonomy and mortality in frail or pre-frail patients [24]. However, few studies have focused on the outcome of robust and pre-frail elderly patients compared to frail elderly ones as proposed in this trial. Once again, the concept of frailty transcends comorbidity alone to include strength, function, and cognition, and in many types of surgery, frailty status predicts postoperative complications better than traditional risk scores. This line of study is crucial for the elderly, especially for those with frailty symptoms. This study will provide information on the outcomes of pre-frail patients to determine if pre-frail patients may benefit from a pre-habilitation program to increase their physical function. This active program could help them become more robust and may lead to a better outcome.

This concept of patient optimization was initially described in patients with respiratory functions that limited surgery. Specifically, Gillis et al. in Montreal demonstrated a significant improvement in physical function after a 4-week program that included aerobic/anaerobic exercises, nutrition, and psychological support [25]. However, literature on pre-frail patients is scarce. Moreover, a complete psychometric examination aims to discriminate risk factors of cognitive dysfunction, loss of autonomy, and postoperative delirium. This examination could detect factors that should be investigated before a major intervention using a limited questionnaire. Indeed, the time devoted to presurgery in the elderly is limited in many countries, and additional tools are required to improve their postoperative care. Accordingly, this represents another objective for this large cohort of elderly patients. In a recent study, Revenig et al. demonstrated in 351 consecutive patients undergoing major intra-abdominal interventions that shrinking and grip strength alone hold the same prognostic information as the full five-component Fried frailty criteria for 30-day morbidity and mortality [5]. The addition of the ASA score and serum hemoglobin creates a composite risk score, which facilitates the classification of patients into discrete low, intermediate (odds ratio (OR) 1.974, 95% CI 1.006–3.877, *p* = 0.048), and high (OR 4.889, 95% CI 2.220–10.769, *p* < 0.001) risk categories, with a corresponding stepwise increase in risk for 30-day postoperative complications [5]. The use of muscle assessment is also a novel concept for patients with sarcopenia. Indeed, this loss in muscle mass and in performance largely impairs the daily life of patients, and some studies suggest a correlation between sarcopenia, which is measured through paravertebral muscle mass, and lumbar spine L3. This simple preoperative exam provides new information that should promote caution during the postoperative course [26].

The main limitation to our approach is the use of anesthesia in both groups using the BIS sensor, which is available at any moment for both groups. This could also lead to the optimization of the control group compared to the standard group. However, in the case of special morbidity as in elderly patients, this was the only way to make this comparison. Secondly, volatile anesthetics are not used in this study and may induce a different response. Thirdly, we have no knowledge of the rate of frail patients in the operating room, as surgeons can spontaneously reject an operation when faced with a patient with several comorbidities.

If our hypothesis is true, automated anesthesia could be recommended to maintain a similar frailty status among the elderly.

### Trial status

The inclusion of the patients and data started early in 2016. To date, the first 50 patients have been included and randomized and followed during at least 3 months. The patients’ pathway is now optimized to ensure follow-up and appropriate reporting of the data, and new centers will be opened shortly.

## Abbreviations

ADL: Activities of daily living
ASA: American Society of Anesthesiologists
BIS: Bispectral index
EEG: Electroencephalogram
EKG: Electrocardiogram
IADL: Instrumental activities of daily living
OR: Odds ratio
